**Methods:**

A multicenter, observational study of 215 vaccine-naïve patients with clinically recovered COVID-19, studied at 3–6 months following infection, and 133 healthy volunteers without prior SARS-CoV-2 infection. Patients with recovered COVID-19 were screened for long COVID related symptoms and their impact on daily living. Multi-organ, multi-parametric magnetic resonance imaging (MRI) and circulating biomarkers were acquired to document sub-clinical organ pathology. All participants underwent pulmonary function, aerobic endurance (6 min walk test), cognition testing and olfaction assessment. Clinical outcomes were collected up to 1 year from infection. The primary objective of this study is to identify associations between organ injury and disability in patients with long-COVID symptoms in comparison to controls. As a secondary objective, imaging and circulating biomarkers with the potential to exacerbate cardiovascular health were characterized.

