## Methods and analysis

### Study design

This is an observational prospective case–control study of patients in Alberta with recovered COVID-19 from the first 2 waves of the pandemic and age- and sex-matched healthy control participants without prior COVID-19 infection. Institutional approval was obtained from the health research ethics boards at the University of Alberta for the study of patients with recovered COVID-19 (Pro00102389), the two supplementary studies (Pro00109391, Pro00110221) and the healthy controls (Pro00110706) and at the University of Calgary for patients with recovered COVID-19 (REB21-0035). The study was also registered at clinicaltrials.gov (MOIST late cross-sectional study; NCT04525404). All patients provided written informed consent. The Canadian VIGOUR Centre (thecvc.ca) helped provide project management, and the study team vouches for the data integrity and analyses of the study. Patient related variables were captured in REDCap (Research Electronic Data Capture) hosted at the University of Alberta and imaging data was stored in a secure server in the department of biomedical engineering at the University of Alberta. The principal investigator ([name]) oversaw site monitoring and data management and will supervise all analyses related to the study.

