### Participant selection

Adult patients within 3 months of COVID-19 illness and prior to the availability of m-RNA vaccination, were recruited from October 2020 to July 2021. Patients with COVID-19 illness requiring hospitalization were identified prospectively at the University of Alberta hospital and retrospectively by the regional health authority, Alberta Health Services. Interested patients with less severe COVID-19 illness also contacted the study team following advertisement on the internet, mainstream media and personal communication. All patients required documentation of COVID-19 infection on nasal or oropharyngeal swab polymerase chain reaction testing within the last 6 months. Healthy controls without prior COVID-19 infection were also recruited from July 2021 to July 2023. Normative brain imaging and cognitive testing were collected separately from healthy control participants prior to the pandemic (19). Control participants with a history of cardiovascular disease or cardiovascular risk factors were excluded. No participants had contraindication to MRI and all provided informed consent after a review of the study objectives, procedures and potential risks and benefits.

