### Magnetic resonance imaging

A multiparametric, non-contrast research MRI was performed at 3 T (Magnetom Prisma, Siemens Healthineers) at the Universities of Alberta and Calgary with a total scan time of approximately 75 min (Figure 2). Image analysis for cardiac and non-cardiac data was performed at core lab facilities within the University of Calgary and University of Alberta, respectively.

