*Brain*: After repositioning the participant into a 64 channel head RF coil, four different images were acquired of the brain over 24 min: (i) 3D fluid attenuation inversion recovery (FLAIR) for lesion detection (1.0 mm isotropic, 5 min), (ii) 3D T1-weighted MPRAGE for regional brain volumes (0.85 mm isotropic, 3.5 min), (iii) 2D high-resolution diffusion tensor imaging (DTI) for identifying strokes/cytotoxic edema and microstructure in white matter mainly (1.5 mm isotropic, 10 b0/6 b500/20 b1000/64 b2500 s/mm^2^, 9.5 min), and 3D multi-echo, gradient recalled echo (0.9 × 0.9 × 1.7 mm^3^, 6 TE from 3.8–31 ms, 5.5 min) for quantitative susceptibility mapping (QSM) and transverse relaxation rate (R2*) for micro-bleeds and sensitivity to iron/myelin, particularly in deep gray matter. The latter three images match previous protocols of a healthy cohort (19).

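### Patient–control MRI contrasts are fixed as unadjusted tests although site may differ by group, and the control source for brain, cognition and FLAIR lesions is unclear

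*Protocol article*

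**What the plan says.** **Sites.** The Study design section gives Alberta approval for patients and the supplementary studies "and the healthy controls (Pro00110706) and at the University of Calgary for patients with recovered COVID-19 (REB21-0035". Scanning was "performed at 3 T (Magnetom Prisma, Siemens Healthineers) at the Universities of Alberta and Calgary", not split by group. Reading was divided by organ: "Image analysis for cardiac and non-cardiac data was performed at core lab facilities within the University of Calgary and University of Alberta, respectively".

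**Periods.** Under Participant selection, patients "were recruited from October 2020 to July 2021" and controls were recruited from July 2021 to July 2023. The Introduction dates the patient study to August 2021.

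**Brain and cognition.** Participant selection adds: "Normative brain imaging and cognitive testing were collected separately from healthy control participants prior to the pandemic". The abstract says: "All participants underwent pulmonary function, aerobic endurance (6 min walk test), cognition testing and olfaction assessment". The legend to Figure 1 also depicts functional testing and MRI for everyone. The brain paragraph of the MRI section lists four acquisitions in the order FLAIR, MPRAGE, DTI and multi-echo gradient echo, then says: "The latter three images match previous protocols of a healthy cohort".

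**Outcomes and analysis.** Table 1 places cognitive testing and a lesion metric drawn from FLAIR and DTI among the organ-injury measures, which Study outcomes calls primary. The Statistical plan compares patients with controls by t-test or Mann–Whitney test for continuous variables and chi-square or Fisher's test for categorical ones. No site, age, sex or period term is included.

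**The concern.** A two-group test attributes every systematic difference between the groups to COVID. If part of the patient group was scanned on a second machine and the controls were not, the mean difference in T1, T2 or fat fraction includes a share of the between-scanner offset. Calendar time acts in the same way through software changes or drift.

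The brain and cognitive outcomes raise a separate question: who the controls are. The Table 3 controls were recruited from July 2021, so they cannot be the pre-pandemic normative cohort. If that cohort is the comparator, Table 3 does not describe it. If both sources are used, the article does not say which serves which outcome. At stake is the comparison with healthy controls in the primary objective, which names the brain among its organs.

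**Working it through.** The article states no power, effect size or SD, and the target of 200 and 100 was set empirically. There is therefore no figure of the plan to reproduce. The check sets the text side by side and then illustrates scale.

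**1. Period.** Patient recruitment, October 2020 to July 2021, spans 10 calendar months. Control recruitment, July 2021 to July 2023, spans 25. The overlap is 1 month, or 2 if the patient study is taken to August 2021. Group and period are almost completely confounded.

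**2. Brain sequences.**

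| Acquisition | Matched to normative cohort? | Table 1 brain metric |
|---|---|---|
| FLAIR | not listed as matched | lesions |
| MPRAGE (T1-weighted) | yes | volume |
| DTI | yes | lesions |
| Multi-echo gradient echo | yes | susceptibility and iron |

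Only the FLAIR part of the lesion metric lacks a documented matched comparator.

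**3. Scale of a site effect (illustration only).** Assumptions, none of them in the documents:
- all controls scanned at Alberta;
- a share f = 10–40% of patients scanned at Calgary;
- a between-site T1 offset d = 5–20 ms;
- a myocardial T1 SD σ = 30–50 ms;
- two-sided testing at 0.05 (the article does not state sidedness).

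Formulas, with the 215 patients and 133 controls of Table 3:
- bias b = f × d
- se = σ × √(1/215 + 1/133) = 0.1103 σ
- chance of p < 0.05 with no COVID effect = Φ(b/se − 1.96) + Φ(−b/se − 1.96)

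| σ (ms) | f | d (ms) | b (ms) | Type I error |
|---|---|---|---|---|
| 50 | 10% | 5 | 0.5 | 5.1% |
| 40 | 25% | 10 | 2.5 | 8.8% |
| 40 | 40% | 20 | 8.0 | 44.2% |
| 30 | 40% | 20 | 8.0 | 67.6% |

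Worked example, second row: se = 0.1103 × 40 = 4.41; b/se = 2.5/4.41 = 0.567; Φ(−1.393) + Φ(−2.527) = 0.082 + 0.006 = 0.088.

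For scale, the patient–control T1 differences quoted under Sample size calculation are 1,125 − 1,082 = 43 ms and 1,033 − 1,008 = 25 ms. The difference by prior hospitalization is 1,141 − 1,119 = 22 ms. The assumed biases are smaller than all three.

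**4. Scale of a period effect (same formula).** A drift shifts the whole control group, so f drops out. A shift of 5 ms with σ = 50 gives 14.8%, and 10 ms with σ = 30 gives 85.6%.

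**5. What a site term can do.** If all controls are at Alberta, there are three cells: Alberta patients, Calgary patients and Alberta controls. A model with group and site then estimates the COVID effect as Alberta patients minus Alberta controls. Calgary patients contribute only to the residual variance and to the age and sex slopes. The standard error, at equal σ, grows by the factor √(1/(215(1−f)) + 1/133) ÷ √(1/215 + 1/133). This is 1.02 at f = 10%, 1.06 at 25% and 1.12 at 40%.

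**The case against.** Several stronger readings are tempting, and the documents do not support them.

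- **Controls were scanned at one site.** A reader might infer this from the approvals sentence. That sentence says which board approved which study, not where anyone was scanned. The inference is plausible but unstated.
- **Group is fully confounded with site.** Even on the single-site reading, patients were studied at both universities, so the confounding is partial and separable. A common scanner model and reading divided by organ, not by group, reduce the risk further without removing it.
- **The historical cohort had no FLAIR, so a primary outcome has no comparator.** The text says only which images match; a FLAIR with other settings may exist. DTI gives the lesion metric a matched component, and comparisons across symptom severity need no external control.
- **The 133 controls had no brain MRI or cognitive testing.** The abstract and the Figure 1 legend point the other way, and the normative data could be supplementary. What stands is an ambiguity to be reconciled, not a proven contradiction.
- **Acquisition effects exceed disease effects.** A reader might compare the healthy groups of the two cited cardiac studies (1,082 and 1,008 ms). One is a median and the other a mean, from unrelated studies. They say nothing about two scanners of one model in one study.

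It is also fair to say that a site covariate is often left to an analysis plan, which is not shown here. That answers an omission, but this article names the patient–control test, so the unadjusted comparison is a stated choice.

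**Conclusion.** The concern holds in a limited form. The near-absence of calendar overlap, the separate pre-pandemic source of normative brain and cognitive data, the absence of FLAIR from the matched sequences and the unadjusted tests are all in the text. Single-site scanning of controls is an inference, and the site-bias argument depends on it.

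No size can be put on the site bias from the documents; the figures above only show what assumed inputs would do. Period is the better-documented confounder, and no model can remove it with one or two shared months. One caveat applies: the dates are mainly recruitment dates, so the overlap in scan dates could differ somewhat. The brain point is narrow: the FLAIR component has no documented matched comparator, and the control cohort for brain and cognition must be named. These changes should be made before the patient–control analyses are run.

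**What to change.** 1. Replace the unadjusted patient–control MRI tests with models containing group, site, age and sex. Table 3 already shows imbalance: mean age 51 against 47 years, and 65% against 51% women. Repeat the contrasts in Alberta-scanned participants only.
2. State for each outcome which control cohort is used and where it was scanned. Give the number, age and sex of the historical cohort.
3. Reconcile the Participant selection sentence on normative data with the abstract and the Figure 1 legend.
4. Use age- and sex-adjusted models for any brain or cognitive contrast against the historical cohort.
5. Analyse FLAIR lesions only within patients, by symptom severity, unless the 133 controls have matched FLAIR.
6. State that the control period barely overlaps the patient period, so scanner drift cannot be adjusted away and limits the conclusions.

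The cost is analysis and wording only, with no new data. Under the assumed Calgary shares, intervals widen by about 2–12% if all controls are at Alberta. The FLAIR lesion contrast with controls may be lost.

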### Participant selection

Adult patients within 3 months of COVID-19 illness and prior to the availability of m-RNA vaccination, were recruited from October 2020 to July 2021. Patients with COVID-19 illness requiring hospitalization were identified prospectively at the University of Alberta hospital and retrospectively by the regional health authority, Alberta Health Services. Interested patients with less severe COVID-19 illness also contacted the study team following advertisement on the internet, mainstream media and personal communication. All patients required documentation of COVID-19 infection on nasal or oropharyngeal swab polymerase chain reaction testing within the last 6 months. Healthy controls without prior COVID-19 infection were also recruited from July 2021 to July 2023. Normative brain imaging and cognitive testing were collected separately from healthy control participants prior to the pandemic (19). Control participants with a history of cardiovascular disease or cardiovascular risk factors were excluded. No participants had contraindication to MRI and all provided informed consent after a review of the study objectives, procedures and potential risks and benefits.

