## Abstract

**Introduction:**

Short-term clinical outcomes from SARS-CoV-2 infection are generally favorable. However, 15–20% of patients report persistent symptoms of at least 12 weeks duration, often referred to as long COVID. Population studies have also demonstrated an increased risk of incident diabetes and cardiovascular disease at 12 months following infection. While imaging studies have identified multi-organ injury patterns in patients with recovered COVID-19, their respective contributions to the disability and morbidity of long COVID is unclear.

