## Introduction

The coronavirus disease (COVID)-19 pandemic has caused significant worldwide death and disability, particularly prior to the widespread availability of vaccine. Since the start of the pandemic, there have been seven waves of COVID-19 caused by evolving variants of the Severe Acute Respiratory Syndrome coronavirus-2 (SARS-CoV-2) (1, 2). In Canada, the province of Alberta, a region with 4.5 million inhabitants, has consistently had the highest seroprevalence for SARS-CoV-2 and in November 2023 approximately 85% had evidence for prior infection (3). However, the immediate health risk from acute infection has been low with a hospitalization rate of 5.5% and death in 1% (4).

While the short-term prognosis of COVID-19 is excellent, the intermediate and long-term health risks are of greater concern. A 2022 national survey found that approximately 17% of Canadians with COVID-19 report persistent symptoms lasting greater than 12 weeks, a syndrome referred to as long COVID or post COVID condition (5, 6). Symptoms are often characterized by fatigue, shortness of breath and/or cognitive impairment, with a disproportionate effect in women (5). Among affected individuals, 47% reported symptoms lasting at least 1 year and 21% described symptoms that often or always limited daily activities. The national survey also found that 27% of patient with SARS-CoV-2 developed long COVID following the Alpha variant infection compared to 13% with the Omicron variant (5).

Furthermore, population health studies have shown that COVID-19 confers a 50–70% excess risk of incident cardiovascular disease and diabetes mellitus in the first 12 months (7, 8). These health risks appear greater in patients with long COVID (9). The mechanism(s) responsible for long COVID and the increased cardiometabolic risk are not well understood and there is a lack of high-quality evidence-based studies guiding management.

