The prevailing etiologic mechanisms proposed for long COVID include immune dysregulation, autoimmunity and immune imprinting, endothelial dysfunction and thrombosis, impaired neurological signaling and effects on the host microbiome (10). However, knowledge on pathogenesis remains limited and there is an important unmet need for rigorous preclinical and clinical studies in long COVID. Given the systemic (i.e., multi-organ) nature of both acute phase COVID-19 illness and long COVID, knowledge has been gained from whole body imaging. Magnetic resonance imaging (MRI) is a safe (non-ionizing radiation), non-invasive imaging technique that provides detailed information on tissue changes including injury. MRI has been used as an alternative to computed tomography for the characterization of pulmonary disease following severe COVID-19 pneumonia (11). MRI derived measures of visceral adipose tissue and liver fat are also strongly associated with risk of hospitalization from COVID-19 independent of body mass index (12). Whole body MRI-based studies of patients with recovered COVID-19 have identified subclinical multi-organ involvement (13–15). In an MRI study of 201 patients with long COVID, mean age 45 years, organ damage was identified in 70%, including the pancreas in 45%, liver in 29% and heart in 24% (14). In this study, MRI evidence of organ impairment was defined as a non-contrast T1 time (longitudinal relaxation time) greater than normal reference values. Several cardiac MRI based studies of patients with recovered COVID-19 have found evidence of subclinical myocardial inflammation (16–18), however, the clinical significance of this finding is not well established.

We undertook a multicenter, prospective study of patients in Alberta with recovered COVID-19 from October 2020 to August 2021 to characterize symptom burden, functional impairment and end-organ damage by MRI. We hypothesized that the extent of tissue injury on MRI would be associated with patient reported disability and objective measures of functional performance.

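### The recruitment, PCR and visit time windows are left unreconciled, the 3-month floor for the visit appears only in the abstract, and the planned symptom and MRI analyses take no account of time since infection

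*Protocol article*

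**What the plan says.** The protocol article gives three time limits for the recovered patients, each with a different starting point.

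- **Recruitment** (Participant selection), counted from illness: "Adult patients within 3 months of COVID-19 illness", between October 2020 and July 2021. No lower limit is given.
- **Proof of infection** (same paragraph), counted back from a date that is not named: "swab polymerase chain reaction testing within the last 6 months".
- **Study visit** (Abstract, Methods), counted from infection: "studied at 3–6 months following infection". Neither Participant selection nor the description of the testing day in Data collection and analysis repeats this.

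The Introduction dates the study of recovered patients "from October 2020 to August 2021".

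Long COVID is described by duration. The abstract has "persistent symptoms of at least 12 weeks duration, often referred to as long COVID", and the Introduction has "persistent symptoms lasting greater than 12 weeks".

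According to Data collection and analysis, symptoms are rated at the same visit as the functional tests and MRI, and the timing of the illness is recorded. The Statistical plan then compares organ-injury measures across four symptom-severity groups by one-way analysis of variance, and relates MRI to functional performance by Pearson correlation. Neither analysis carries a 12-week condition or a term for time since infection.

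**The concern.** The symptom groups are meant to represent lasting illness, and what makes a symptom lasting here is the 12-week mark. Symptoms are rated at the visit, so the earliest permitted visit decides whether ordinary convalescence can enter the symptomatic groups. That limit stands only in the abstract. The selection text, which a reader would consult for eligibility, has two upper limits that differ (3 and 6 months), no lower limit, and no interval from recruitment to visit.

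The second issue does not depend on early visits. If symptoms and tissue measures such as T1 both decline as infection recedes, patients seen sooner would tend to have more of both. An unadjusted comparison could then show an association between symptoms and MRI that comes partly from timing. The article gives no data on such a decline, so this is a plausible route and not a demonstrated one. It bears on the central question, because the study's hypothesis links the extent of MRI injury to disability and functional performance.

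**Working it through.** No sample size, power or significance figure is at stake. The check is whether the windows fit together and whether they keep visits beyond 12 weeks.

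**Conversion** (1 month = 365.25/12 = 30.44 days)
- 3 months = 91.3 days = 13.0 weeks. The shortest run of three calendar months is 89 days = 12.7 weeks.
- 6 months = 182.6 days = 26.1 weeks.
- 12 weeks = 84 days.

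**Can one patient meet all three limits?** Take recruitment on day 60 and the visit on day 120.
- Recruitment: 60 ≤ 91.3, met.
- Visit: 91.3 ≤ 120 ≤ 182.6, met.
- PCR, if the swab was taken around day 0: under 182.6 days old on both dates, met.

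So the limits are compatible when attached to different events. If recruitment and visit were the same day, the 0–3 and 3–6 month windows would meet only at about day 91.

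**Does the stated visit window protect the 12-week mark?** Yes. Its lower end (91.3 days, or 89 at the shortest) exceeds 84, so no part of it lies before 12 weeks.

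**What would the selection text alone permit?** The documents give no distribution of visit times. As an illustration only, and assuming visits spread evenly over a window, the share before day 84 would be:

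| Window taken to govern the visit | Share before day 84 |
|---|---|
| 3–6 months (abstract) | 0% |
| 0–6 months (PCR limit only) | 84/182.6 = 46% |
| 0–3 months (visit at recruitment) | 84/91.3 = 92% |

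These are shares of window length, not estimates of how many patients were seen early.

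**Calendar check**, assuming the last visit was on 31 August 2021 (the article gives no last-visit date):
- 31 August minus 84 days is 8 June 2021. Anyone ill after that date could not have reached 12 weeks by the last visit.
- A patient recruited on 31 July has 31 days left, so must already have been 91.3 − 31 = 60.3 days from illness to be seen at 3 months.
- A patient recruited on 1 July has 61 days left, so needed 91.3 − 61 = 30.3 days.

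Both figures lie inside the 3-month recruitment limit. The schedule is feasible but tight, and the selection text does not require those minimum intervals.

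**Variation in timing if the window was kept.** Days since infection would still run from about 91 to 183, a twofold range, with no term for it in either planned analysis.

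**The case against.** A reader might infer that the three windows contradict each other and that patients seen at, say, 6 to 10 weeks are being analysed as long COVID. The documents do not support that. The limits attach to recruitment, PCR and visit, and one patient can satisfy them all. The only window stated for the visit is the abstract's, written in the past tense about the 215 patients, and it starts beyond 12 weeks. The selection criteria do not govern visit timing.

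The calendar argument is also limited. 31 August is an assumed last visit. No late recruit enrolled soon after illness is documented, and Study design restricts patients to the first two pandemic waves, although the article does not date them. The 8 June arithmetic is right, but it shows only that the selection text would not exclude an early visit.

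Finally, a condensed article may leave visit scheduling and covariates to the full protocol or analysis plan, and the figure showing recruitment is not available here. That is a fair reason not to treat missing detail as an error in itself.

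Most of this stands, and it removes any claim of contradiction or of known misclassification. It does not remove the rest. The article itself states the limits with different starting points and does not say how they relate. It also names the analyses, and as named they are unadjusted for time.

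**Conclusion.** The concern holds in a limited form. The windows are unreconciled, not incompatible. Participant selection has a 3-month upper limit at recruitment, a 6-month PCR limit with no reference date, and no minimum interval to the visit, while the 3-month floor that protects the long COVID definition stands only in the abstract.

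The number of visits before 84 days is not given. It is zero if the abstract's window was enforced and unknown otherwise, and nothing in the article shows that any occurred.

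The analytic consequence applies either way. Time since infection can differ about twofold between patients and enters neither the symptom-group comparison nor the MRI–function correlations. Whether this biases them depends on the unproven assumption that symptoms or function and tissue measures both change over that period. The size of any bias cannot be worked out from the article. The point is worth acting on because the check is nearly free and removes no one if the window was kept.

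**What to change.** 1. Reconcile the abstract's Methods with Participant selection by stating one window with one reference date, counted from the positive PCR to the study visit, with its lower and upper ends.
2. Report the distribution of days from PCR to visit, including how many visits, if any, fell before 84 days.
3. Add days since PCR as a covariate in the comparison across symptom-severity groups (ANCOVA or regression), and use partial correlation for MRI against functional performance. This applies within the recovered patients only, since the controls have no infection date.
4. If any visit fell before 84 days, run the long-COVID symptom analysis in patients seen at 84 days or later, and show the result in all 215 as a sensitivity analysis.

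The cost is a text correction, one extra model term and possibly a few patients leaving the main symptom analysis. No new data collection should be needed, because PCR documentation was an entry requirement and illness timing is recorded. This assumes that the PCR and visit dates were kept.
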